### Trial outcomes

Follow-up will continue until all women have completed at least 18 months of participation and the average length of follow up for the whole sample is at least three years. Data and safety monitoring issues are addressed in a specific section below. Strategies for maximizing adherence to the Study have been developed. Outcomes are assessed at baseline, then generally again at 6 months, and then annually. (Table 3)

**Table 3 Tab3:** Measurements used to determine trial outcomes

Measurements	Times of measurement during follow up^a^	Main outcomes
Exams		
75 g oral glucose tolerance test	6 months, annual	Diabetes/intermediate hyperglycemia [57]; insulin resistance [69]
Glycated hemoglobin	6 months, annual	Diabetes [57]
HDL-C, triglycerides	6 months, annual	Metabolic syndrome [78]
Weight	6 months, annual	Weight loss/maintenance
Height		
Blood pressure, heart rate (Omron 765CP, Omron, Kyoto, Japan)	6 months, annual	Metabolic syndrome [78]
Waist and hip circumferences	6 months, annual	Metabolic syndrome [78]
Abdominal height (Holtain-Kahn caliper, Seritex, Tinton Falls, NJ, United States)	6 months, annual	
Percent body fat (InnerScan BC-1500,Tanita)	6 months, annual	
Handgrip strength (Jamar hydraulic hand dynamometer); 6 min walking test; sit and reach test (Wells bench, Wood-WCS)	6 months, annual	
Accelerometry (ActiGraph WGT3X)	6 months, annual	Reaching 7500 steps/day [75]
Questionnaires		
Quality of life [62]	Annual	
Depressive symptoms (Edinburgh questionnaire) [79]	6 months, annual	
Perceived body image [64] and diabetes risk [66]	Annual	
Sleep quality (Pittsburg questionnaire) [80]	Annual	
Breastfeeding status	6 months, 1 year	Duration of exclusive and overall breastfeeeding
Dietary recall/registry	6 months, annual	
Physical activity and sedentary behavior (IPAQ long version, leisure-time and transportation sections [58]; sedentary behaviors questionnaire) [59–61].	6 months, annual	

^a^All taken at baseline

Primary Outcome: The primary outcome is incident type 2 diabetes, which will be ascertained by OGTT and HbA1C in both groups. At study close-out, all women whose last ascertainment occurred more than 6 months previously will be reassessed.

Secondary Outcomes:Normalization of intermediate hyperglycemia (fasting and 2 h blood samples, HbA1C) [57]Metabolic syndrome (fasting blood samples, questionnaires) [78]Mean insulin resistance, beta cell function (OGTT) [69]Mean weight loss and weight goal achievementPhysical fitness (6 min. test [67], handgrip; sit and reach test)Duration of breastfeeding and rate of exclusive breastfeeding up to 6 months postpartum (phone interviews between 6 months and 1 year postpartum)Quality of life [62]Mean body fat/central fat (weight, % body fat, waist circumference and abdominal height)Sleep quality (Pittsburg questionnaire) [65]Perceived body image (questionnaire) [64]Depressive symptoms (Edinburgh questionnaire) [63]Infant growth (reference curves)Adverse events

Process outcomes:Dietary quality (dietary recalls)Intensity and duration of physical activity (Number of minutes spent in moderate to vigorous intensity activity and the number of minutes spent in sedentary activity, estimated by accelerometer; and percentage of women achieving the moderate or vigorous physical activity goal of 150 min/week, estimated by the leisure-time and transportation sections of the International Physical Activity Questionnaire - IPAQ, long version [58])Percentage of women adhering to the protocol of intervention (phone sessions and outcome monitoring)Participation in optional activities: group sessions and social events.

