### Baseline measurements and trial enrollment

At baseline, women respond to a standardized questionnaire and undergo physical measurements. Data on prenatal care and delivery are extracted from the health care record carried by the participant. Questionnaires address risk factors for type 2 diabetes, including eating and drinking behaviors, physical activity [58], sedentary habits [59–61] as well as issues such as quality of life [62], depressive symptoms [63], perceived body image trajectories [64], quality and duration of sleep [65], medication use, and perceived risk of diabetes [66]. A physical examination includes blood pressure, waist and hip circumferences, weight, height, body composition, fitness assessment [67] and abdominal height [68]. Additionally, physical activity is assessed using accelerometers (ActiGraph GT3X) worn on the waist for seven days.

A standardized 75 g OGTT [57] is done with samples taken at fasting and 30, 60, 90 and 120 min [69]. A urine sample is collected upon arrival. Aliquots of serum, plasma, urine and DNA are stored for future measurements. To assure that women who used insulin during pregnancy and had not undergone a postpartum OGTT have not developed diabetes, their fasting and 2 h glucose values are determined prior to randomization. After key aspects of the clinical trial protocol are reviewed and remaining questions are clarified, an additional written informed consent is obtained and a further visit to the clinic is scheduled.

At this second baseline visit, women complete exams, including a six minute walking test. After eligibility has been once more confirmed (including the absence of diabetes), and key aspects of the protocol, including randomization, have been reviewed, women are enrolled into the trial.

Participants missing the scheduled visits are rescheduled when justified. Missing three appointments is a criterion for exclusion from the clinical trial. In this sense, these preparatory visits also serve as a run-in period for the trial.

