### Key aspects of the intervention

Intervention is tailored so as to meet the particular needs of women with previous GDM during their postpartum. Building from social cognitive theory [70], interventions are participant-centered [71–73], allowing adaptation to each women’s setting, within the limits of a standardized prevention program with defined goals and structure. Communication strategies are based on motivational interviewing [14] and health coaching approaches implemented in the primary care setting [74].

The specific components of the intervention and corresponding goals are:Promotion and support for exclusive breastfeeding for up to six months of life and partial breastfeeding thereafter for at least three additional months.Stimulation and support for personally-monitored weight loss and maintenance with the goal of returning to pre-pregnancy weight and, for those overweight or obese pre-pregnancy, losing at least an additional 5 % of body weight. If this goal has already been achieved at randomization, the treatment goal will be a loss of 5 % of current body weight or that needed to achieve a BMI of 22.5 kg/m^2^.Promotion of healthy eating, emphasizing avoidance of ultra-processed foods, limited intake of oils, sugars and processed meats, increased intake of foodstuffs in their natural state, regular intake of water and dairy products, and intake of coffee and tea without sugar or sweeteners.Encouragement and support for a personally-monitored progressive increase in physical activity with an initial goal of breaking up extended bouts of sitting with ambulatory activity, reduction of sedentary behavior (defined as <5000 steps/day); and later striving to perform at least 150 min of moderate or vigorous physical activity/week (7500 steps/day with at least 30 min. taken at a cadence of 100 steps/min.) [75–77].

Table 1 summarizes the progressive nature of the lifestyle interventions which takes into consideration the particularities of recent motherhood, the gradual changes promoted, and the allowance of participant-centered approaches in the progression towards the final goals.

**Table 1 Tab1:** Progressive nature of lifestyle interventions for weight control, healthy eating and an active lifestyle

	Stage 1	Stage 2	Stage 3
	8-12 weeks	8 a 26 weeks	Up to close out

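### The process outcomes take attainment of the coached 150 min/week activity goal from self-report and omit the device-measured 7500 steps/day outcome in Table 3

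*Protocol article*

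**What the plan says.** The activity item under Process outcomes (Trial outcomes section) has two parts with different sources. The first is objective: "Number of minutes spent in moderate to vigorous intensity activity and the number of minutes spent in sedentary activity, estimated by accelerometer". The second is the percentage of women who reach 150 min/week, and it comes from self-report: "estimated by the leisure-time and transportation sections of the International Physical Activity Questionnaire", long version.

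Table 3 schedules both instruments at baseline, 6 months and annually. The questionnaire row reads "Physical activity and sedentary behavior (IPAQ long version, leisure-time and transportation sections [58]; sedentary behaviors questionnaire" and has no main outcome beside it. The accelerometry row does have one, "Reaching 7500 steps/day [75". That steps outcome does not appear in the process or secondary outcome lists.

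The same goal is what the intervention arm is coached towards. Key aspects of the intervention describes "Encouragement and support for a personally-monitored progressive increase in physical activity", ending at 150 min/week. According to Intervention groups, coached women are also encouraged to record their steps, while controls receive printed materials that include physical activity recommendations. Blinding to allocation is stated in the Follow-up section only for the staff who measure glucose.

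**The concern.** A woman who has been coached by phone towards a threshold, and is then asked about the activity that decides whether she passed it, has a reason to round up. A woman given a booklet has less reason. The article does not say that participants are unblinded, but coaching against a booklet cannot be concealed from them. Over-reporting is therefore likely to differ by arm, in the direction that favours the intervention.

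What is at stake is interpretation. The Objectives section includes learning what makes prevention succeed or fail, and attainment of the activity goal is a natural input to that. A reported gain in attainment without a gain in activity would mislead on which component worked. The device is already scheduled at the same times, and a device-based attainment measure already stands in Table 3, yet the only attainment percentage among the process outcomes is the self-reported one.

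**Working it through.** **1. The plan's own figures.** The article states no figure for this outcome. Its sample size rests on diabetes events alone and reproduces: hazard ratio ln(0.85)/ln(0.75) = 0.565; 134.5 events (stated: 135) for four evenly spaced looks with symmetric O'Brien-Fleming boundaries; event probability 0.1827, so N = 135/0.1827 = 739 (stated: 740). No activity measure enters these figures.

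**2. The versions of the goal side by side.**

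| Place | Form of the goal or outcome | Source |
|---|---|---|
| Key aspects of the intervention | 150 min/week, restated as 7500 steps/day with at least 30 min at 100 steps/min | target, no instrument named |
| Table 1 | 150 min/week, or 7500 steps/day; no cadence condition | target, no instrument named |
| Table 3 | 7500 steps/day; no cadence condition | accelerometer |
| Process outcomes | 150 min/week | IPAQ, leisure-time and transport sections only |

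These can give different attainment rates. The questionnaire version covers two domains of activity, a limit that the goal itself does not carry. The cadence condition appears in one place out of three that mention steps. Read as applying on all seven days, it amounts to 30 × 7 = 210 min/week; on five days it is 30 × 5 = 150.

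**3. How much misreporting would matter.** The article gives neither attainment nor misreporting rates, so this step is an illustration over a range. Assume:
- no true difference between arms;
- true attainment p in both arms;
- a fraction q of coached non-attainers who report attainment, and accurate reporting by controls;
- n = 370 per arm (740 allocated 1:1).

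Reported attainment in the coached arm is p + q(1 − p), so the spurious difference is Δ = q(1 − p). The chance of two-sided p < 0.05 is approximately Φ((Δ − 1.96·SE₀)/SE₁), with SE₀ pooled and SE₁ unpooled.

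Worked case, p = 0.40 and q = 0.10:
- coached arm 0.40 + 0.10 × 0.60 = 0.46, so Δ = 0.06;
- SE₀ = √(2 × 0.43 × 0.57/370) = 0.0364;
- SE₁ = √((0.40 × 0.60 + 0.46 × 0.54)/370) = 0.0363;
- Φ((0.06 − 0.0713)/0.0363) = 0.377.

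| True attainment | q = 5 % | q = 10 % | q = 20 % |
|---|---|---|---|
| 20 % | 4.0 points, 26 % | 8.0 points, 72 % | 16.0 points, 99.8 % |
| 30 % | 3.5 points, 17 % | 7.0 points, 52 % | 14.0 points, 98 % |
| 40 % | 3.0 points, 13 % | 6.0 points, 38 % | 12.0 points, 91 % |
| 50 % | 2.5 points, 10 % | 5.0 points, 28 % | 10.0 points, 78 % |

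The nominal chance is 5 %. With 300 women per arm, to allow for losses, the ranges are about 9 to 22 %, 23 to 63 % and 69 to 99 %. The table shows how sensitive the measure is to misreporting. It does not show that misreporting will occur.

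**The case against.** The strongest reply is that objective measurement is already planned. Moderate-to-vigorous minutes by accelerometer stand in the same process outcome, and Table 3 has a device-based attainment outcome. If coached women over-reported without changing, the device results would show no matching difference and the discrepancy would be visible. This stands, and it is why the point is minor. It does not explain why the attainment percentage among the process outcomes is the self-reported one.

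A reader might infer more than the article supports:
- *The trial could credit activity with an effect that it did not have, and nothing would reveal it.* The accelerometer minutes are a check against this.
- *Goal attainment is the measure that explains the trial's result.* The Objectives section names no measure, and this is one part of one process outcome.
- *Seven-day device data exist at every visit.* The wear period is stated for baseline only ("physical activity is assessed using accelerometers (ActiGraph GT3X) worn on the waist for seven days"). Table 3 gives follow-up times, not duration of wear.
- *Controls get no activity message.* Their printed materials include one.

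Two further objections also stand. A 150 min/week cut-off on questionnaire minutes cannot simply be moved to accelerometer minutes, because the two capture different activity and the device needs an intensity cut-point. Nor is the device free of arm-related bias: women know that they are wearing it, only the coached arm is encouraged to record steps, and both wear and behaviour during wear may differ by arm.

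**Conclusion.** The point holds as a minor one about a process outcome. As written, attainment of the coached goal is fixed to self-report in a trial whose participants know their arm, and the device-measured steps outcome of Table 3 is missing from the process outcomes. The expected direction of bias favours the intervention. Its size is unknown: over the assumed range the spurious difference runs from 2.5 to 16 percentage points, with a chance of nominal significance from about 10 % to above 99 %. This rests on assumed attainment and misreporting rates, and on the inference from the design that participants are unblinded. Incident diabetes, the 135 events and the 740 women are unaffected.

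**What to change.** In the process outcomes:
- Make accelerometer-based attainment the leading activity-goal measure, using the 7500 steps/day outcome already in Table 3.
- State once, in the same way in Key aspects of the intervention, Table 1, Table 3 and the process outcomes, whether the cadence condition is part of the definition. The passages need to be reconciled; this review does not choose between them.
- If 150 min/week is also to be derived from the device, state the intensity cut-point and the minimum-wear rule in advance.
- Keep the IPAQ percentage as supportive, and report both measures by arm.

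The cost is wording and a short definition, since the device data are already scheduled. The downside is that women with too little wear time are missing for this measure, and wear may differ by arm. Reporting the number with valid wear in each arm would let readers judge that.

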### Follow-up

The timeline of study activities during recruitment and the clinical trial is shown in Table 4. Follow-up of those not entering the trial is also included in the table.

**Table 4 Tab4:** Timeline of main activities from recruitment to the end of the clinical trial

Activity	Recruitment for the trial and follow-up of those not entering the trial					Clinical trial						
	Pregnancy	Perinatal period	Post-pregnancy period (weeks)									
	Recruitment	Telephone contact	Trial preparation	Baseline measures	Follow-up^a^	All women entering the trial						
						Post-randomization follow-up (months)						
	Gestational weeks 20–40	Pregnancy to 30 days postpartum	4–104	8–104	Up to 260	0	0–6	6–12	12–24	24–36	36–48	48–60
Consents	x			x								
Entry	x	x	x			Trial randomization						
Interviews/exams/chart reviews	x			x		x		x	x	x	x	x
Phone contacts		x	x		x							
Baseline and follow-up measurements				x				x	x	x	x	x
Material distributions	Breastfeeding folder 1; Pregnancy to postpartum booklet	Mail at birth: Breastfeeding folder 2		Project folder		Preventing diabetes booklet						
						Intervention group						
Motivational interviews						x	x	x	x			
Phone sessions							x	x	x	x	x	x
SMS texting							x	x	x	x	x	x
Group sessions							As needed					
Social events							As needed					
Mailings							As needed					

^a^Follow-up of those not entering the trial

At trial follow-up visits, glucose determinations are performed by staff blinded to patient allocation. Principal investigators, clinical staff, outcome assessors and participants are blinded with respect to glucose results for the duration of the trial. Women who reach diabetes glucose levels are notified. Given that follow up the participants occurs at yearly intervals, we do not require confirmation of the diabetes status on another day to ascertain incident diabetes in order to avoid an excessive length of time prior to the initiation of medical care for diabetes.

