### Recruitment and eligibility

All women aged 18 or older identified as having GDM at pre-natal clinics in selected Brazilian cities, regardless of the diagnostic criteria, and living within distance permitting an easy access to the trial sites, are invited to participate.

At first contact, the study protocol is explained and an initial signed consent is obtained. Information regarding socio-demographics, reproductive history, pre- and early gestational weight, gestational age, GDM diagnosis and treatment as well as dietary, physical activity and smoking habits is obtained through interviews and chart review. Folders regarding the importance of preventing diabetes and of breastfeeding are distributed. If recruited during pregnancy and the immediate postpartum period, women are monitored monthly by telephone until eligible to begin the trial. Date and place of birth are obtained and intention to breastfeed evaluated. Additionally, we inquire about the use of insulin and or oral antidiabetic medication during later pregnancy and obtain the last measured pregnancy and postpartum weights.

Although entrance is permitted up to 2 years postpartum, eligible women are encouraged to enter the trial as early as 10 weeks after pregnancy. Those who used insulin during pregnancy are automatically eligible. Eligibility for remaining women is assessed by a 2 h 75 g oral glucose tolerance test (OGTT) performed after the sixth postpartum week. Women presenting impaired fasting glucose (fasting plasma glucose ≥ 100 mg/dl; 5.6 mmol/L) or impaired glucose tolerance (2 h plasma glucose ≥ 140 mg/dl;7.8 mmol/L) [57] on this testing are eligible.

The following exclusion criteria apply:confirmed diabetes (two abnormal OGTTs), [57] or one OGTT with unequivocal values [abnormal fasting *and* 2 h plasma glucose values; fasting plasma glucose ≥140 mg/dl (7.8 mmol/L) or 2 h glucose ≥270 mg/dl (15 mol/L)];current use of antidiabetic medication;normal glucose tolerance (if not using insulin during pregnancy);an indication that the trial interventions are not feasible, for example, due to relocation to a place distant from the trial site or a poor response in previous contacts (e.g., lack of interest in phone interviews);a body mass index ≥ 40 kg/m^2^; andhealth limitations or treatments (assessed by questionnaire) which would restrict the nutritional intervention or the ability to practice physical activity, affect glucose tolerance or limit participation or survival.

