### Ethical issues

The trial protocol was approved by the ethics committee of the Hospital de Clínicas de Porto Alegre (Project 120097, May 4, 2012). Written consent is obtained at initial recruitment and then again, before enrollment to the trial. At randomization we explain to the participants that they will have equal chances of being entered into one or the other group. We also explain that it is not known whether applying a more intense intervention relatively soon after postpartum is more beneficial than the conventional approach. However, if the Study finds that it is indeed more beneficial, then at study close-out those who did not receive the more intense approach will be informed about how to undertake the activities found to be successful. While we emphasize the importance of maintaining participation throughout the study so as to minimize bias in the trial results, women are informed that they may request to terminate participation if they so decide. Those who drop out of the study will nevertheless have their available follow-up time included in analysis of treatment effects. Women found to have developed diabetes will be notified and oriented to seek medical attention to confirm diagnosis and initiate treatment.

A data and safety monitoring board (DSMB) will monitor efficacy (or futility) and adverse effects. Based on these considerations, the DSMB may recommend that the protocol be modified or that the LINDA trial be terminated. The DSMB will consist of experts in relevant biomedical fields, biostatistics and medical ethics.

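### Diabetes must be confirmed to keep a woman out but not to count as an event, so the written rules allow some women already in the diabetic range at baseline to be scored as incident cases

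*Protocol article*

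**What the plan says.** **Entry.** In Recruitment and eligibility, the diabetes exclusion is "confirmed diabetes (two abnormal OGTTs), [57] or one OGTT with unequivocal values". Unequivocal means that fasting and 2 h values are both abnormal, or fasting glucose is at least 140 mg/dl, or 2 h glucose is at least 270 mg/dl. HbA1c is not among the criteria. The glycaemic route to eligibility is "impaired fasting glucose (fasting plasma glucose ≥ 100 mg/dl; 5.6 mmol/L) or impaired glucose tolerance (2 h plasma glucose ≥ 140 mg/dl" and upwards, with no ceiling other than that exclusion. Women who used insulin in pregnancy are eligible automatically.

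**Re-check.** In Baseline measurements and trial enrollment, for insulin users without a postpartum OGTT, "their fasting and 2 h glucose values are determined prior to randomization". For all women, enrolment follows at the second baseline visit: "After eligibility has been once more confirmed (including the absence of diabetes". No separate definition of absence is given there.

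**Outcome.** In Trial outcomes: "The primary outcome is incident type 2 diabetes, which will be ascertained by OGTT and HbA1C in both groups". Table 3 lists diabetes against both the OGTT and HbA1c, at 6 months and annually, with the footnote "All taken at baseline". In Follow-up: "we do not require confirmation of the diabetes status on another day to ascertain incident diabetes". The reason given is that visits are yearly and that confirmation would delay medical care.

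**After notification.** In Ethical issues: "Women found to have developed diabetes will be notified and oriented to seek medical attention to confirm diagnosis and initiate treatment". Nothing says that the result of that outside confirmation returns to the endpoint.

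**The concern.** The rule is strict for calling a woman diabetic before randomisation and lenient afterwards. A woman in the gap between the two rules can become an incident case without any change in her status. Such an event is prevalent rather than incident, and randomised treatment had little chance to prevent it.

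Three things are at stake:
- The hazard ratio is pulled towards 1.
- The planned 90% power is not fully delivered, because the sample-size calculation treats every event as carrying the design hazard ratio of 0.565.
- These events can be scored from the 6-month visit on, so they fall early and weigh more in the first interim looks, where a futility boundary also applies.

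The reason given for waiving confirmation concerns how soon a woman is told and referred. It does not settle how the endpoint is classified: she can be notified at once and classified separately. The reference to yearly visits also sits awkwardly with the 6-month OGTT in Table 3, though that is a minor point of wording.

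**Working it through.** **1. Who falls in the gap.**
- Women who did not use insulin have an eligibility OGTT and a baseline OGTT. Abnormal on both means two abnormal OGTTs, so they are excluded. Those left in the gap have one abnormal, non-unequivocal result and one that is not abnormal.
- Insulin users may have the baseline OGTT as their first postpartum test. A single abnormal, non-unequivocal result is then not two abnormal OGTTs, and the written rule does not exclude them. This is the clearest route.
- Women with a diabetic-range HbA1c but no excluding OGTT are not excluded. Whether HbA1c alone makes an event is inferred from Table 3; the text joins OGTT and HbA1c without saying whether either suffices.

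**2. Reproducing the plan's figures (Sample size).** Inputs: 3-year incidence 25% v 15%, one-sided 0.025, 90% power, four equally spaced analyses with symmetric O'Brien-Fleming efficacy and futility boundaries, 5% annual drop-out, 18 recruits a month, mean follow-up three years.
- HR = ln(0.85)/ln(0.75) = 0.565.
- Numerical integration over the four looks gives a final critical value of 2.003 and a required drift of 3.311. Events = 4 × 3.311² / (ln 0.565)² = 134.5, so 135. Power at 135 events is 90.1%.
- Exponential hazards with the stated accrual and drop-out give N = 738.9 for 135 events, so 740.

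The plan's arithmetic is sound. What follows changes only the assumption that every event is incident.

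**3. Effect of carried-over events.** The number affected is not in the documents. Assume a share p of the 740 is affected, with HR 1 for their events. With T total events, of which G are genuine, the average log HR is approximately (G/T) × ln 0.565, and the drift is (√T/2) × (G/T) × 0.571. Power is then read from the boundaries in step 2.

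- *A, replacing:* final analysis fixed at 135 events, all affected women test positive again. T = 135, G = 135 − 740p.
- *B, adding:* follow-up runs to the time-based end in Trial outcomes (every woman at least 18 months, mean at least three years), all test positive again. G = 135(1 − p), T = G + 740p.
- *C, adding, half test positive again:* the other half behave as ordinary participants. G = 135(1 − p/2), T = G + 370p.

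| p | Women affected (740p) | A: HR, power | B: G / T, HR, power | C: power |
|---|---|---|---|---|
| 1% | 7.4 | 0.58, 87% | 133.7 / 141.1, 0.58, 88% | 89% |
| 2% | 14.8 | 0.60, 82% | 132.3 / 147.1, 0.60, 86% | 88% |
| 3% | 22.2 | 0.62, 77% | 131.0 / 153.2, 0.61, 84% | 87% |
| 5% | 37.0 | 0.66, 65% | 128.3 / 165.3, 0.64, 80% | 85% |

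Example, p = 2%, case A: G/T = (135 − 14.8)/135 = 0.890; HR = exp(0.890 × ln 0.565) = 0.60; drift = (√135/2) × 0.890 × 0.571 = 2.95; power 82%.

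**4. Cross-check.** A simulation at N = 740 with follow-up to a fixed end, one final test and no interims (600 runs each) gave power of about 87, 88 and 80% for p = 0, 2 and 5%. Monte Carlo error is about 1.5 points, so the first two do not differ. The observed HR rose from 0.58 to 0.60 and 0.66. This is closer to B than to A.

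**The case against.** The strongest reply is that the protocol states its choice openly, gives a reason, and errs on the conservative side. Misclassification that is equal in both arms makes a benefit harder to show; it does not produce a false one. That stands, and it limits the severity.

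The re-check before enrolment is also a real safeguard: insulin users have their glucose read before randomisation and absence of diabetes is confirmed again. This narrows the gap but does not close it, because that section gives no definition of its own and the only written one is the confirmed-diabetes criterion.

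A reader might infer more than the text supports in three respects:
- That women above the outcome threshold at baseline *are* randomised and scored. The rules allow this; the documents do not show how often it happens, and a woman must test positive again to be counted.
- That one HbA1c result certainly makes an event. No either/or rule or cut-off is given, and Follow-up speaks of glucose levels. A condensed article may leave the endpoint algorithm to the full protocol. The OGTT route does not depend on this.
- That power falls to 65%. This needs 5% affected, every one testing positive again, no treatment effect on their events, and a final analysis held to exactly 135 events. The time-based end of follow-up makes the adding case at least as plausible.

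**Conclusion.** The point holds in limited form. The entry and outcome definitions of diabetes differ in the text, and the re-check before enrolment does not reconcile them. As written, part of the incident outcome may be prevalent, with a hazard ratio diluted towards 1 and less than the stated 90% power.

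The size is uncertain. For 1 to 5% of women affected, power is about 87 to 65% in the least favourable reading (fixed 135 events, all testing positive again), 88 to 80% if the events add, and 89 to 85% if they add and only half test positive again. The share affected, the proportion testing positive again, and the HR of 1 are all assumptions; the last is a worst-case simplification, since the intervention may normalise some of these women.

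Type I error is not inflated, and a positive result would remain valid. This is something the sponsor should fix, not a defect that must be cured before the trial can be relied on.

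**What to change.** 1. Reconcile Recruitment and eligibility, Baseline measurements and trial enrollment, Trial outcomes and Follow-up, so that the same definition of diabetes establishes its absence before randomisation and ascertains the outcome. State the role of HbA1c in both. Which diagnostic rule to adopt is for the sponsor.
2. Randomisation began in January 2015, so for women already enrolled, pre-specify before the first interim look an analysis leaving out those whose pre-randomisation baseline values already meet the outcome definition. Membership is fixed before allocation, so the comparison stays unbiased. Report it alongside the all-randomised analysis.
3. Add a sensitivity analysis that counts an event only if same-visit measures are concordant or the protocol's own unequivocal values are met. Do not use agreement of the next scheduled test: notified women are sent for confirmation and treatment, so that test may be taken on treatment, and events found at close-out have no next test.

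**Cost.** Wording in the protocol and analysis plan. The OGTT and HbA1c are already taken at baseline and at the 6-month and annual visits, so no new measurement is needed. A few women become ineligible or leave the restricted analysis set, with slightly fewer events.
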